### Procedures

#### Study interventions

The description of the interventions is as follows:*Intervention 1 (I1)*: the HRV behavior of the participant will be evaluated without exposure to any recovery technique or any type of stress. The follow-up period will be 2 h*Intervention 2 (I2)*: the HRV behavior of the participant will be evaluated before the application of the massage technique. Evaluations will be performed 2 h after massage application*Intervention 3 (I3)*: the HRV behavior of the participant will be evaluated before the implementation of the stress protocol. The autonomic modulation of heart rate will be evaluated 2 h after the end of the stress protocol*Intervention 4 (I4)*: the HRV behavior of the participant will be evaluated before the stress protocol, followed immediately by the massage technique, as well as 2 h after the completion of the massage in order to observe if HRV is anticipated*Intervention 5 (I5)*: the HRV behavior of the participant will be evaluated before the stress protocol, and the massage technique will be applied at the exact moment of ANS recovery, determined by the study of Almeida et al. [11] who used the same stress protocol, and posteriorly there will be follow up for 2 h in order to see if there is potentiation of HRV recovery

The first three interventions of the study (I1, I2, and I3) will be performed to establish the basal behavior of the study variables and/or before the two different stimuli (massage and stress), and for possible explanations and discussion of the study.

In Interventions 4 and 5, analysis of the effects of massage on post-exercise recovery, and the comparison of the effects of massage when performed immediately after stress or 1 h after stress, will be performed.

It is emphasized that at I5 the massage will be applied 60 min after the end of the stress protocol, as this was the exact time identified in the study by Almeida et al. [11] for the recovery of the internal control functions of the body after the same stress protocol as used in the present study.

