### Statistical analysis

For analysis of the data of the population profile, the descriptive statistical method will be used and the results presented as values of means, standard deviations, median, minimum and maximum numbers, and confidence interval. The normality of the data will be evaluated through the Shapiro-Wilk test.

The comparisons of cardiorespiratory parameters and HRV indices between interventions (I1, I2, I3, I4, and I5) and moments (rest (R1) vs recovery moments (R2–R12)), the data are analyzed from the prism of the covariance analysis (ANCOVA), which will be adjusted for the baseline value of the evaluated variable and generated estimated means after such adjustment (extracting the variance explained by the confounding variables). The Levene test will be used to prove the homogeneity of the variances at the created moments, and the Bonferroni post hoc test will be used for comparison. To guarantee homogeneity of data the variable can will be transformed into logarithm.

For analysis of the moments (rest vs recovery moments), repeated measures ANOVA with the Tukey post test for parametric distribution or Friedman test with Dunnett’s post test for non-parametric distribution will be used and the analysis of the different groups will be performed by means of one-way ANOVA with the Tukey post test or the Kruskal-Wallis test with Dunnett’s post test.

The level of significance will be *p* < 0.05 for all tests. The SPSS statistical program (version 13.0) (SPSS Inc., Chicago, IL, USA) will be used for the analyses. Data integrity will be monitored by regularly scrutinizing data files for omissions and errors. Participants will be given an anonymous study ID to protect confidentiality, and only study investigators will have access to the final trial data set.

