### Contribution and clinical applicability

With the accomplishment of this study we will verify which HRV indices demonstrate a significant influence of the massage in post-exercise recovery, and which moment of application presents better recovery after exercise. The data obtained in the present study will provide subsidies for the best management of application of the technique in sports clinical practice, considering periods of training and, mainly, of competitions.

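### No contrast with the stress-only session (I3) is named as the test of massage, and follow-up starts about 12 min (I4) or 72 min (I5) later after stress than in I3

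*Protocol article*

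**What the plan says.** The Background asks whether massage given straight after stress anticipates autonomic recovery, and whether massage given once recovery has occurred potentiates it.

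The Study interventions section gives each session a role. I1, I2 and I3 "will be performed to establish the basal behavior of the study variables" and the response to each stimulus, and also serve "for possible explanations and discussion of the study". The massage question is placed elsewhere: "In Interventions 4 and 5, analysis of the effects of massage on post-exercise recovery". The only comparison named in that sentence is the one on timing: "the comparison of the effects of massage when performed immediately after stress or 1 h after stress, will be performed".

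The Statistical analysis section is wider. It plans "The comparisons of cardiorespiratory parameters and HRV indices between interventions (I1, I2, I3, I4, and I5) and moments", adjusted for baseline, and states that "the Bonferroni post hoc test will be used for comparison". It then adds a second family of tests: "For analysis of the moments (rest vs recovery moments), repeated measures ANOVA", or Friedman, within the session.

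The Contribution section promises to report "which HRV indices demonstrate a significant influence of the massage in post-exercise recovery". It does not say against what that influence is measured.

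**The concern.** HRV moves back towards its resting value after exercise whether or not anyone is massaged. A return to rest within I4 or I5 therefore says nothing about massage. I4 against I5 speaks to timing but cannot show that either massage does anything. Only I3 supplies the missing reference: the same man after the same stress, unmassaged.

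Two things are at stake:

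- The sections disagree about what I3 is for. The text therefore does not commit the trial to the one comparison that answers its question, and it leaves the uncontrolled rest-versus-recovery tests available as apparent support.
- Even when I3 is used, its recovery windows do not appear to start from the same point after stress as those of I4 and I5. Natural recovery could then be credited to massage inside what looks like a controlled comparison.

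**Working it through.** **1. Which contrasts are planned.** Five interventions give 5 × 4 / 2 = 10 pairs. I4–I3 and I5–I3 are two of the ten in the Bonferroni step. They are present but not singled out. The Study interventions section points to I4 and I5 alone. The rest-versus-recovery tests compare R1 with R2–R12 and contain no second condition.

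**2. The clock.** Inputs:

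- Massage lasts 12 min (Massage protocol).
- The I5 massage is given 60 min after the end of stress (Study interventions).
- I3 follow-up is counted from the end of stress, and I4 follow-up from the end of massage. In I5 the 2 h follow-up comes after the massage (Study interventions).
- R2 starts at minute 0 of recovery and R12 at minute 115 (Primary outcome).

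Time since the end of stress = window start + offset. Ignoring transfers, the offset is 0 for I3, 12 for I4, and 60 + 12 = 72 for I5.

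| Window | I3 (min) | I4 (min) | I5 (min) |
|---|---|---|---|
| R2 | 0 | 12 | 72 |
| R7 | 40 | 52 | 112 |
| R8 | 50 | 62 | 122 |
| R9 | 60 | 72 | 132 |
| R11 | 90 | 102 | 162 |
| R12 | 115 | 127 | 187 |

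At any one R label, I4 has 12 min and I5 has 72 min more natural recovery than I3, and I5 has 72 − 12 = 60 min more than I4.

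**3. Is this the right reading of time zero?** The Primary outcome section does not define it. Two points support counting from the end of massage. The Secondary outcomes section lists a separate pre-massage hour of readings in I5, on top of the 2 h of recovery. And if the windows ran from the end of stress in every session, I4's R2, R3 and part of R4 (minutes 0 to 12) would fall during the massage itself, while I5 would have only 120 − 72 = 48 min after massage instead of 2 h.

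**4. What a common clock leaves.** Follow-up spans, in minutes after stress: I3 0–120, I4 12–132, I5 72–192.

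- I4 with I3: 12–120, or 108 min.
- I5 with I3: 72–120, or 48 of I5's 120 min. I5's R2 to R7 lie inside I3 follow-up (R7 ends at 117); R8 to R12 lie beyond it.
- I4 with I5, both after massage: 72–132, or 60 min.

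The fixed-minute readings cannot be re-cut, but they nearly align. I5 recovery minutes 10, 20, 30 and 40 fall at 82, 92, 102 and 112 min, against I3 readings at 80, 90, 100 and 110, so 2 min apart.

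**5. Does naming two contrasts cost sample size?** The plan's own figure first: n = 2(1.960 + 0.842)² × (38.8/26.9)² = 2 × 7.849 × 2.080 = 32.7, so 33, as stated. This is the formula for two independent means. With two contrasts at 0.025 each:

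- If 38.8 is the SD of within-person differences (an assumption), a paired t-test needs 23 men; power is 96% at 36 and 98% at 40.
- If 38.8 is a between-person SD, the two-group formula gives 40 (normal) or 41 (t).

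For all ten pairs at 0.005 the corresponding figures are 32 men, or 56 and 58. None of these covers six indices and eleven windows.

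**The case against.** The strongest reply is that the Statistical analysis section governs. It compares all five interventions with Bonferroni post hoc tests, so the controlled comparison is already planned, and designating one contrast as decisive can be left to a full analysis plan. The Study interventions sentence may mean only that I4 and I5 are the sessions in which massage follows stress. Describing behaviour under stress alone is itself a reference role for I3.

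Much of this stands. A reader might infer from the session descriptions that I3 is kept out of the analysis and used only in discussion. The document does not support that: I3 is in the ANCOVA, and its first stated role is to establish behaviour. A reader might also infer that recovery will be called anticipated when I4 stops differing from rest, or does so at an earlier window than I3. No section states such a rule, so no false-positive rate can be attached to it.

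What does not stand is that the Statistical analysis section settles the matter. It does not say which of its two families of tests carries the claim. Followed by R label, its I3 contrasts inherit the offset shown above. That is a matter of what the article states about follow-up, not of detail left out.

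**Conclusion.** The point holds in a limited form. The right comparison is within the planned analyses but is not designated, and the session roles point away from it. The rest-versus-recovery tests cannot support a claim about massage.

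The more consequential part is the clock. By R label, I3 would be compared with sessions that are about 12 min (I4) or 72 min (I5) further into natural recovery, and the timing comparison would carry about 60 min in I5's favour. If HRV is still recovering over those periods, the bias favours massage, and later massage most.

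This rests on counting recovery from the end of massage in I4 and I5, with transfers ignored. The text supports that reading, but the Primary outcome section does not state it, and the study design figure is not shown. How large the bias is in HRV units cannot be worked out from the document, which gives no recovery curve.

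**What to change.** Align the Study interventions, Statistical analysis and Contribution sections as follows:

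- State time zero for R2–R12 in each session.
- Judge the effect of massage on recovery by the baseline-adjusted, within-participant contrasts I4 minus I3 and I5 minus I3, at equal time since the end of stress.
- Judge timing by I4 minus I5 on the same clock.
- Label the within-session rest-versus-recovery tests as descriptive, supporting no claim that massage anticipates or potentiates recovery.

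The cost is small but goes beyond wording. HRV windows must be re-cut from the RR recordings to a common clock, which assumes the recordings are continuous over follow-up. Fixed-minute readings have to be paired at the nearest time. I5 minus I3 exists only from about 72 to 120 min after stress; later I5 windows have no I3 counterpart and become descriptive. No extra session is needed, because the same men attend all five. Forty men are ample for two contrasts on SDNN if 38.8 is a within-person SD. If it is not, the number is only just enough by the normal formula and one short by the t formula, before withdrawals. Those last two figures are for uncorrelated sessions; positive correlation within a man would lower the requirement.

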### Procedure details

#### Stress protocol

Participants will be submitted to a stress protocol consisting of a jumping program and a maximum short-term cycling test [11]. The jumping program consists of 10 sets of 10 jumps with a 1-min interval between sets. During the jump, participants will be instructed to place their hands on their hips and during the jump landing to flex their knees at 90° in order to avoid compensations. After the jump, the participants will have 1 min of rest and then perform the Wingate anaerobic test protocol, which will be performed on a cycle ergometer Biotec 2100 (Cefise, Nova Odessa, Brazil). The test consists of a 5-min warm-up and the test itself. During warm-up the participant will pedal at a speed of 60 to 90 rpm with a fixed load of 1.0 kg, and in the second and fourth minutes the participant will be required to perform a sprint, reaching the maximum possible speed according to individual perception. After the 5-min warm-up the anaerobic test will be performed, consisting of maximum pedaling for 30 s with a stipulated load of 0.075 kp·kg^-1^ of the participant’s body mass. During the sprints and test, verbal stimuli will be provided to stimulate maximum performance.

This stress protocol was chosen due to the study of Almeida et al. [11] which investigated the protocol and concluded that it is effective in triggering derangements in the ANS. Immediately after completion of the protocol, participants will be directed to a stretcher, where they will lie down to perform the massage immediately after stress (I4) or 1 h after stress (I5), or to remain at rest (I1, I2, and I3), and then be followed up for 2 h to capture the RR intervals.

It is worth mentioning that after the stress protocol all participants will be required to drink 180 ml of water in order to standardize hydration and avoid the influence of blood volume on the results of the present clinical trial.

#### Massage protocol

According to a recent systematic review with meta-analysis [19], the effects of massage seem to be better when it is applied for between 5 and 12 min. Thus, the massage in the present protocol will have a total of 12 min duration, being 6 min on the anterior region of the thigh (3 min for each limb) and 6 min on the posterior region of the trunk. The choice of these anatomical sites was due to the effort required by the stress protocol and location of the preganglionic neurons of the ANS, respectively.

For massage on the anterior thigh (quadriceps femoris muscle) the participant will be placed in the dorsal decubitus and the massage initiated on the dominant limb and then the non-dominant limb, and posteriorly, in the ventral decubitus position, massage will be performed on the trunk (paravertebral muscles). The techniques of surface and deep slip will be used, the latter being presented at two intensities, moderate or intense, being gradually increased. The massage will be performed towards the muscle fibers, from distal to proximal and following the lymphatic flow.

The massage will be performed by three physiotherapists specializing in sports physiotherapy, previously trained by a sports physiotherapist with 10 years’ experience in sports massage.

A pilot study will be conducted for the training of the physiotherapists who will apply the massage in a standardized manner regarding the intensity, rhythm, form of application of massage, and application dynamics through data collection. The physiotherapists will be required to present excellent correlations between them in order to be eligible to perform the technique.

The massage will have the rhythm: 1 s of slip and 1 s for return of the hand to the initial position, totaling 2 s of slip (Table 1). The rhythm of the massage will be controlled by an electronic metronome that will only be used by the therapists during performance of the technique.

**Table 1 Tab1:** Massage protocol for the anterior thigh region and posterior trunk region

Anatomical site	Slip	Pressure	Rhythm	Time (seconds)	Total slips per technique
Anterior thigh	Surface	Light	1 slip every 2 s	60	30
	Deep 1	Moderate	1 slip every 2 s	60	30
	Deep 2	Intense	1 slip every 2 s	60	30
Posterior trunk	Surface	Light	1 slip every 2 s	120	60
	Deep 1	Moderate	1 slip every 2 s	120	60
	Deep 2	Intense	1 slip every 2 s	120	60

Besides standardization of the intensity and rhythm of the massage performed by the physiotherapist, in order not to cause discomfort and possible pressure variations in the application of the technique, participants will be required to report their level of comfort from a scale that considers the technique as “light,” “moderate,” or “intense,” corresponding, respectively, to surface slip, deep 1 slip, and deep 2 slip. Details of the massage protocol can be seen in Table 1.

### Participant timeline

The time schedule of enrollment, interventions, and assessments is outlined in Fig. 3. Recruitment of study subjects started in April 2018.

**Fig. 3 Fig3:**
[figure not shown]
Content for the schedule of enrollment, interventions, and assessments

### Outcomes

The primary outcome will be the evaluation of autonomic modulation of heart rate by means of HRV. Secondary outcomes are cardiorespiratory parameters (blood pressure, heart rate, respiratory rate, and oxygen saturation) and individual touch perception. Evaluations will be performed by the same independent trained assessors throughout the study.

#### Primary outcome

HRV will be used as the primary outcome as it is an important overall marker of post-exercise recovery [16]. The HRV analysis will be performed from the series of RR intervals captured by the cardiofrequency meter Polar Electro Oy – model V800, and linear methods analyzed in the time domain and frequency domain, and Poincaré plot. All HRV indices will be obtained through the *software* Kubios HRV – version 2.0 [20].

For this analysis, the time series of RR intervals will initially be subjected to digital filtering using the *software* Kubios HRV – version 2.0, supplemented by manual filtering, to eliminate premature ectopic beats and artifacts, and only series with more than 95% of sinus beats will be included in the study [20]. Through visual analysis of the time series, the absence of ectopic artifacts or beats that can interfere in the HRV analysis will be observed.

During the recovery period, the evaluated moments will be: R1 (initial 5 min of rest before performing the interventions), R2 (initial 5 min of recovery), R3 (fifth to 10th minutes of recovery), R4 (10th to 15th minutes of recovery), R5 (20th to 25th minutes of recovery), R6 (30th to 35th minutes of recovery), R7 (40th to 45th minutes of recovery), R8 (50th to 55th minutes of recovery), R9 (60th to 65th minutes of recovery), R10 (70th to 75th minutes of recovery), R11 (90th to 95th minutes of recovery), and R12 (115th to 120th minutes of recovery). It is worth mentioning that 256 consecutive RR intervals will be obtained at these moments [21].

HRV indices in the time domain (rMSSD and SDNN), frequency domain (low-frequency spectral component (LF) and high-frequency spectral component (HF)), and the Poincaré plot (SD1 and SD2) will be evaluated [22].

In the time domain, the rMSSD Index corresponds to the square root of the square mean of the differences between the adjacent normal RR intervals in a time interval expressed in milliseconds and evaluates the behavior of the parasympathetic autonomic modulation [22], while the SDNN Index represents the standard deviation of all normal RR intervals recorded in a time interval, expressed in milliseconds, and is considered a measure of global variability, that is, it evaluates both sympathetic and parasympathetic modulation [22].

In the frequency domain the low-frequency spectral component (LF – frequency between 0.04 and 0.15 Hz) is considered an index that evaluates sympathetic and parasympathetic behavior [22, 23], while the high-frequency spectral component (HF – frequency between 0.15 and 0.4 Hz) is a marker of vagal modulation [22, 23]. The spectral analysis will be calculated from a tachograph using the fast Fourier transform algorithm.

The Poincaré plot is a map of points in Cartesian coordinates constructed from the values of the RR intervals obtained [22]. For quantitative analysis of the plot an ellipse will be adjusted to the points of the graph where the indices SD1 and SD2 are obtained. SD1 is an instantaneous index of beat-to-beat variability and represents the parasympathetic modulation [24], while the SD2 Index represents the HRV in long-term records, and reflects the overall variability [24].

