### Analysis population

The criteria that define the exclusion of the participant in the final analysis of the data will be: intercurrences during the execution of the protocols that prevent their continuity, absence from more than 80% of the proposed sessions, and capture errors in the RR intervals.

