### Sample size

As described above the primary outcome will be the HRV. The sample size calculation was carried out based on the study of Arroyo-Morales et al. [15] in which the SDNN Index of the HRV was selected, since it is an index that expresses the behavior of the ANS in a global way. To establish the sample size, a mean effect of 26.9 and standard deviation of 38.8 were chosen. The level of significance for the sample size is 5%, the power test is 80%, two-tailed test, and 10% of the total value of *n* is added to statistically supply the analyses in the case of withdrawals during data collection. The value obtained for the sample size was 33 participants, adding the 10% gave a sample of 36 volunteers. However, there are other indices besides the SDNN Index within the HRV, and this situation generates an environment where the sample size could be underestimated. In the same sense, due to the new proposal presented by the study, there are no trials in the literature that have the same proposal dynamics, and thus, for safety we will add four volunteers to ensure the statistical analysis of all HRV indices, thus totaling a sample of 40 participants.

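### If the 95% sinus-beat rule is applied per moment, the complete-row tests named for rest versus recovery discard a whole session for one failed window, and the participant-exclusion rule is not reconciled with it

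*Protocol article*

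**What the plan says.** Four places in the protocol article bear on this.

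- **Primary outcome.** It says that "the time series of RR intervals will initially be subjected to digital filtering", followed by manual filtering, and that "only series with more than 95% of sinus beats will be included in the study". The next paragraph lists the 12 moments, starting with "R1 (initial 5 min of rest before performing the interventions), R2 (initial 5 min of recovery" and running to R12, with 256 consecutive RR intervals at each. The article does not define a series as a moment, a recording or all of a man's recordings.
- **Analysis population.** The list introduced by "The criteria that define the exclusion of the participant in the final analysis of the data will be" includes "capture errors in the RR intervals". It gives no threshold, and the unit removed is the participant.
- **Statistical analysis.** For rest versus recovery moments it names "repeated measures ANOVA with the Tukey post test for parametric distribution or Friedman test". For interventions and moments together, "the data are analyzed from the prism of the covariance analysis (ANCOVA), which will be adjusted for the baseline value of the evaluated variable". One-way ANOVA or Kruskal-Wallis is named for the groups. None of these is designated as the primary analysis.
- **Sample size.** The 10% addition "is added to statistically supply the analyses in the case of withdrawals during data collection". Four more volunteers are added because there are several HRV indices and the design is new.

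**The concern.** HRV is the primary outcome, and its return to rest over two hours is what the trial sets out to describe. A quality rule that acts on single windows leaves gaps in men who attend every session. Classical repeated measures ANOVA and the Friedman test cannot use a row with a gap. A man with 11 usable windows and one unusable window then contributes nothing to the time-course analysis for that intervention, although most of his recording is sound.

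The number analysed could also differ between interventions, and the remaining men would be those with uniformly clean recordings. The sample-size allowance was not made for this kind of loss. Read literally, the participant-exclusion rule goes further and removes the man from the final analysis altogether. The article gives no way to tell which rule governs a single bad window.

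**Working it through.** **The plan's own figure.** Inputs from Sample size: effect 26.9, SD 38.8, two-sided 5%, power 80%. Two independent means, per group:

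n = 2 × [38.8 × (1.960 + 0.842) / 26.9]² = 32.66, rounded up to 33. Then 33 × 1.10 = 36.3 (stated as 36), and 36 + 4 = 40.

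The stated 33 reproduces. It comes from a two-group comparison and does not size a 12-moment within-session test.

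**Complete sessions under a per-moment filter.** Inputs: 12 moments (Primary outcome), 40 men (Sample size), and a failure probability p per window. The article does not give p, so 1%, 2% and 5% are assumed, equal across moments.

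- Independent failures: 40 × (1 − p)^12.
- Failures clustered within men, assumed intraclass correlation ρ = 0.1 (beta-binomial): with s = (1 − ρ)/ρ = 9 and b = 9(1 − p), 40 × the product over i = 0 to 11 of (b + i)/(9 + i).

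| p | (1 − p)^12 | Complete of 40, independent | Complete of 40, clustered |
|---|---|---|---|
| 1% | 0.886 | 35.5 | 36.9 |
| 2% | 0.785 | 31.4 | 34.1 |
| 5% | 0.540 | 21.6 | 26.7 |

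**Valid data discarded.** The share of valid windows not used is 1 − P(row complete)/(1 − p). At p = 2%:

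- Valid windows expected per intervention: 40 × 12 × 0.98 = 470.4.
- Independent: 12 × 31.39 = 376.7 used, so 20% discarded.
- Clustered: 12 × 34.10 = 409.2 used, so 13% discarded.

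**Orientation only.** Complete rows fall below 33 when p exceeds 1 − (33/40)^(1/12) = 1.6% under independence, or about 2.4% at ρ = 0.1. Because 33 does not size this test, these are reference points and not statements about its power.

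**The two exclusion rules side by side.** Primary outcome admits or rejects a series by a 95% threshold. Analysis population removes a participant for capture errors with no threshold. Neither refers to the other. One failed window could therefore cost a window, a session or a man, depending on which rule is read and how.

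**The case against.** The strongest objection is that the per-moment reading is an inference. Filtering is described as the initial step and the moments are listed afterwards, so a whole-recording reading is equally open. That stands, and the point is conditional for this reason. On the whole-recording reading the filter itself removes the session, and no choice of model recovers it. The unit still has to be defined.

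A second objection is that handling of missing moments is usually left to a statistical analysis plan or full protocol. That is fair as far as silence goes. But the article does fix the two complete-row tests and does state a participant-exclusion rule, and the point rests on those statements.

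Several stronger readings are tempting, and the document does not support them:

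- **That the loss falls on the designated primary analysis.** No analysis is so designated. ANCOVA or one-way tests, if run moment by moment, would lose only the bad window, or the session from the baseline-adjusted ANCOVA if R1 fails.
- **That the loss differs by HRV index.** All six indices come from the same RR series, so a failed series removes all six alike. It can differ by intervention.
- **That all five sessions form one layout of 60 windows.** Statistical analysis plans no such layout.
- **That failures concentrate in R2 and R3 after maximal effort.** This is plausible, but nothing in the article says so, and the calculation assumes equal rates.

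Finally, the size is assumed throughout. At 1% the loss is modest. At 2% with clustering, 34.1 sessions remain.

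**Conclusion.** The point holds in conditional form. If the 95% rule is applied to each moment, the tests named for rest versus recovery use only sessions with all 12 moments valid. Expected complete sessions out of 40 then range from 36.9 (1% failure, clustered) to 21.6 (5% failure, independent). This rests on an assumed failure rate that is equal across moments, and on an assumed intraclass correlation of 0.1 for the clustered figures. Stronger clustering would make the loss smaller.

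Two parts do not depend on any rate: the unit of the 95% rule is undefined, and the participant-exclusion rule is not reconciled with it. The 10% allowance does not cover either kind of loss. The effect is on the precision and representativeness of the time-course analysis of the primary outcome. It does not show that the intervention comparisons fall short of the stated 80% power.

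**What to change.** 1. In Primary outcome, state that the 95% rule is applied to each of the 12 moments separately.
2. In Analysis population, restate the capture-error criterion so that a failed window removes that window and not the man. Without this the next step recovers nothing from the men concerned.
3. In Statistical analysis, replace repeated measures ANOVA or Friedman for the moments with a likelihood-based linear mixed model: random effects for participant and for session within participant, moment as the repeated factor, and the index log-transformed where needed.
4. Report the number of valid windows by intervention and moment, so that readers can see where data were lost.

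The cost is wording and slightly more analysis work, with no extra participants or recordings. The mixed model assumes that failed windows are missing at random given the data observed. The counts in step 4 help readers judge that assumption but cannot prove it.
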